## Abstract

**Background:**

Pharmaceutical practice worldwide is developing towards patient care. Medication Review (MR) and Medication Therapy Management (MTM) are evolving as the most prominent services in pharmaceutical care and have a strong potential to provide a large benefit for patients and society. MTMs can only be performed in an interprofessional, collaborative setting. Several international studies have explored the effects of a MTM on the quality of therapy and costs. For Germany the data is still deficient. This study aims to provide data on the effects of an interprofessional MTM regarding quality of therapy, quality of life, costs and cost-effectiveness.

**Method/Design:**

The study is designed as a cluster-randomized controlled trial in primary care, involving 12 outpatient clinics (clusters) and 165 patients. Primary care units are allocated to interventions using a Stepped Wedge Design. All units are initially assigned to the control group. After a 6 month observation period, general practitioners (GP) are randomly allocated to one of three groups and the interprofessional medication therapy management approach is implemented sequentially per each group with a lag of 3 months between. The primary outcome is the change in the quality of therapy measured by the MAI (Medication Appropriateness Index). Secondary outcomes include changes in the number of drug related problems, medication complexity, changes in drug-adherence, changes in health-status and function, quality of life, direct costs and the incremental cost-effectiveness ratio. The acceptance of the interprofessional Medication Therapy Management approach is assessed by qualitative methods.

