#### Sample size and power calculation

Sample size calculation for the stepped wedge design is based on Woertman et al. [38]. Because there were no studies investigating the effect of Medication Management an effect size of 0.25 is considered as clinically and socially relevant. Based on this assumption and using a two-tailed *t*-test with statistical power of 80 % and significance level alpha = 0.05 a total unadjusted sample size of *N* = 502 is needed. An assumption of 20 patients per practice and little correlation between the clusters (ICC = 0.05) leads to a design factor of 0.383 in the present step wedge model. Adjusting the sample size with the design factor and considering a maximum drop-out rate of 20 % the final sample size is calculated to *N* = 240.

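### The abstract describes 165 patients, but the sample size section needs 240 for 80% power; the gap is unexplained, and at 165 the plan's own inputs give about 64–74%

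*Protocol article*

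**What the plan says.** The abstract (Method/Design) describes the cluster-randomised stepped wedge trial as "involving 12 outpatient clinics (clusters) and 165 patients". It does not call 165 a target, an enrolled number or an analysed number.

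The section on sample size and power calculation works from these inputs:

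- Effect: "an effect size of 0.25 is considered as clinically and socially relevant".
- Test: "using a two-tailed *t*-test with statistical power of 80 % and significance level alpha = 0.05".
- Starting size: "a total unadjusted sample size of *N* = 502 is needed".
- Clustering: "An assumption of 20 patients per practice", with an ICC of 0.05, which "leads to a design factor of 0.383 in the present step wedge model".
- Result: after a maximum drop-out of 20%, "the final sample size is calculated to" 240.

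The Trial status section dates patient recruitment and baseline data collection to September–December 2013. It adds that data cleaning and analysis had just begun when the manuscript was submitted.

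**The concern.** Two sizes for the same trial stand in one article. The cluster count agrees between them, since 12 practices of 20 make 240. The patient count does not, since 165/12 = 13.75 per practice. Nor is 165 an intermediate step of the calculation: it is neither the number to be analysed (about 192) nor the number to be recruited (240).

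The only power in the article is 80%, and it belongs to 240. A reader who takes the size from the abstract and the power from the Methods will credit the trial with more sensitivity than its own inputs support. This matters most if the primary MAI comparison is not significant, because the result could then be read as showing that an effect of 0.25 SD is absent. The actual recruitment figure should have been known at writing, so the authors could have addressed the gap.

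**Working it through.** **Inputs, all from the sample size section unless noted.** Effect d = 0.25 SD; two-sided alpha 0.05 (z = 1.960); power 80% (z = 0.842); design factor DE = 0.383; maximum drop-out 20%; 165 patients in 12 clinics (abstract).

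**Step 1: reproduce the plan's figure.**

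- Unadjusted total = 4 × (1.960 + 0.842)² / 0.25² ≈ 502. Rounding up per arm gives 504, and an exact t-test calculation gives 506. The stated 502 is reproduced within rounding.
- With the design factor: 502 × 0.383 = 192.3 evaluable.
- With drop-out: 192.3 / (1 − 0.20) = 240.3, stated as 240, which also equals 12 × 20.

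The plan's arithmetic therefore holds.

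**Step 2: place 165 against it.**

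- Against the recruitment target: 165/240 = 0.69, or 31% below.
- Against the evaluable number: 165/192 = 0.86, or 14% below.

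The number falls short even if every patient is retained.

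**Step 3: power with the plan's own factor.** With N analysed, the individually randomised equivalent is N/DE, and

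power = Φ(0.25 × √(N/0.383) / 2 − 1.960).

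| N analysed | Meaning | N/0.383 | Power |
|---|---|---|---|
| 192 | the plan's evaluable number | 501.3 | 79.9% |
| 165 | no drop-out | 430.8 | 73.7% |
| 132 | 165 less 20% | 344.6 | 64.1% |

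The first row returns the plan's 80%, so the formula matches the plan's method.

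**Step 4: effect detectable with 80% power** = 2.802 × 2 × √(0.383/N).

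- N = 165: 2.802 × 2 × √(0.383/165) = 0.27 SD.
- N = 132: 2.802 × 2 × √(0.383/132) = 0.30 SD.

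The type II error at 0.25 SD rises from the planned 20% to between 26% and 36%.

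**The case against.** The strongest reply is that nothing is contradictory. The sample size section sets an a priori target, and the abstract of an article submitted after recruitment closed gives what was achieved. A target and an enrolment may differ, and the 80% is an input that yields 240, not a claim about 165. Much of this stands. Achieved enrolment is the most plausible reading of 165, given the Trial status section, and the calculation of 240 is sound. But the article never says that 165 is the enrolment. The abstract gives it as part of the design description, and the Methods present 240 and 80% without qualification. The reader has to guess that the target was missed.

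A second reply is that the low end of the range is pessimistic. This also stands. The plan calls 20% a maximum drop-out. The Statistical analyses section keeps everyone with a baseline MAI score in the full-analysis set and uses a mixed model under missing at random, so patients who leave early still contribute their observed visits. Counting only 132 treats those patients as contributing nothing, so 64% is a lower bound under the plan's inputs. The no-drop-out figure of 74% is still below 80%.

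Third, Fig. 2, the projected recruitment flowchart, was not available for this check. The statement that the two numbers are not reconciled is limited to the visible text.

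**Conclusion.** The point holds: the article gives two unreconciled sizes, and its stated power does not belong to the size in its abstract. On the plan's own inputs, 165 patients give about 64–74% power at 0.25 SD, or an effect of 0.27–0.30 SD detectable with 80% power. This rests on 0.25 SD, two-sided 5%, the printed factor of 0.383 and drop-out between 0 and 20%. It holds whether 165 means enrolled or analysed.

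Three stronger conclusions that a reader might draw are not supported:

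- *That 240 is wrong, or that the article claims 80% power for 165.* The figure of 240 reproduces, and the 80% is attached to it as a design input.
- *That having fewer than 20 patients per practice does further harm through the design factor.* At a fixed ICC, smaller clusters if anything move the factor slightly in the trial's favour. The shortfall comes from the total number of patients.
- *That power is far below 64% because 0.383 may not fit the visit schedule.* The article does not print the formula or the step and measurement counts behind 0.383, so no such figure can be derived from it. The question is separate and is not needed here.

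**What to change.** - Keep 240 in the sample size section as the a priori target, tied to 80% power at 0.25 SD. Both numbers belong in the article, so one should not simply replace the other.
- Label 165 in the abstract as planned or enrolled. If enrolled, say in the sample size or Trial status section that the target of 240 was not reached.
- State the consequence for 165 patients: power of about 74% with no drop-out and not below about 64% at the maximum 20%, or a detectable effect of 0.27–0.30 SD, using the factor of 0.383.
- State that a non-significant MAI result will be interpreted through its confidence interval, by whether it excludes 0.25 SD.

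The cost is a few sentences and the one recalculation shown above. Trial conduct and the analysis model do not change. The stated power becomes less favourable.

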**Discussion:**

The patient interview and brown bag review are activities, typically provided by the pharmacist. In this trial the patient is blinded to the pharmacist. The strength of having the patient blinded to the pharmacists is to exclude skepticism of the patient toward unknown pharmacies, which might be a major confounder in a regional and community setting. A weakness is that some patient related data might reach the pharmacists in a way, which might differ from self-acquired data.

**Trial registration:**

Current controlled trials ISRCTN41595373.

## Background

### Polypharmacy

The care of patients with multiple chronic diseases entails many challenges, in particular related to higher than average coordination and medication complexity. In an European study Fialova et al. found that 51 % of participating patients take more than six prescribed medications per day [1].

Overall, 20 % of GPs’ patients older than 65 years receive 60 % of all prescribed drugs [2]. In fact, polypharmacy comes along with frequently undesirable consequences, such as increased risk of inappropriate drug use, under-use of effective treatments, medication errors, drug interactions, poor patient compliance, and adverse drug reactions [3]. Regarding this, medication management provided by pharmacists may overcome these challenges [4, 5].

### Current interventions and MTM approaches

Pharmaceutical practice worldwide is currently developing towards patient care. Pharmaceutical care has been promoted by Hepler and Strand of the University of Florida in 1990 and has been redefined by the PCNE in 2013/2014 [6, 7]. According to the PCNE definition, pharmaceutical care covers numerous activities to “optimize medicines use and improve health outcomes”. Certain care aspects, like enhanced patient education have been well described and studied: Jalal et al. found patient education, provided by pharmacists beneficial in cardiovascular diseases [8], Schmiedel et al. recently found that patient education can reduce the risk to acquire diabetes [9]. Several studies could support the efficacy of patient counseling on drug-adherence [10] or patient skills in handling drug-devices [11–13].

The WHO and FIP have promoted a patient centered approach by publishing a handbook in 2006 [14]. Medication Review (MR) and Medication Therapy Management (MTM) are evolving as the most prominent services in pharmaceutical care and have a strong potential to provide a large benefit for patients and society. A comprehensive MTM can only be performed in an interprofessional setting [15]. Several international studies have explored the effects of a MTM on the quality of therapy and costs [16, 10, 17, 18]. A systematic review of Nkansah et al. found that the available trials are varying in study design and endpoints and hardly can be compared to services of other health care providers. Hence further studies on Medication Management are desired [19].

The impact of pharmaceutical services widely differs among societies with the setting of the national health care system. Differences in education and collaboration as well as structures and barriers between professions lead to a variety of possible outcomes. For Germany the data supporting a MTM is still deficient.

### Novel aspects of the interprofessional medication therapy management approach

Most studies on MTM are examining certain effects of the intervention of the participating pharmacists and are evaluated by themselves. Pharmaceutical aspects, like a change in drug-adherence or a reduction in drug related problems are assessed [20–22].

Interventions can only reach the patient if they are approved by the decision maker, the general practitioner (GP) or primary care provider (PCP). A consensus between all health care providers is likely to support the therapy. The WestGem-study has a pronounced focus on interprofessional cooperation and collaboration. It might be one of the first Medication Therapy Management studies combining three participating health care professions, consisting of physicians, pharmacists and home-care specialists. The interprofessional approach combines case management routines of the home-care specialists at the patient-site with information gained during the advanced Medication Review by specialised and clinical experienced study pharmacists.

The development of the approach was based on the Medical Research Council (MRC) guideline for the development and evaluation of randomized controlled trials [23, 24]. It was piloted with a group of seven GPs, two pharmacists and two home-care specialists.

### Study aim and objectives

The aim of this randomized controlled trial is to evaluate the application of an interprofessional collaborative Medication Therapy Management approach in multimorbid patients, receiving multiple systemic available drugs. The evaluation refers to the extent of improvement in the quality of drug therapy through examination of drug related problems (DRPs) or drug related events and suggestions on optimizing drug use to reach therapeutic goals. Several tools are used to assess the patients’ drug therapy and home-care needs.

Part of the complex intervention might be the removal of inappropriately prescribed medication, disclosure of drug related problems and prescribing cascades, assessing drug-drug interactions, determination of therapeutic goals, evaluation of pain management, the assessment of chief complaints and quality of life and a reflection of costs and cost-effectiveness of this complex intervention under terms of routine care.

## Methods

### Primary objective

The primary objective of this study is to determine whether the complex intervention would change the quality of medication therapy determined by the MAI (medication appropriateness index) [25, 26] in comparison to standard care. The intervention focuses on multimorbid patients receiving polypharmacy. It is done supplementary to standard care.

### Secondary objectives

Secondary outcomes include changes in the number of drug related problems, classified according to PCNE version 6.2, medication complexity, measured by the MRCI [27], changes in adherence (measured by the Morisky-score [18]), changes in health-status and function, quality of life, direct and indirect costs, and the incremental cost-effectiveness ratio.

### Setting

The study is conducted in a community and outpatient primary care setting in two model regions in North Rhine-Westphalia, located in Western Germany. We have chosen regions with different network structures, which enables us to measure performance and outcomes of the interprofessional medication therapy management approach while taking setting specific influence factors into account.

Outpatient health care in *region A* is organised as a network including GPs (n ≈ 15) and medical specialists (n ≈ 18). Outpatient health care in *region B* does not present in any network structure (number of available GPs in this area is ≈ 55). Local GPs of the *model regions* are contacted by an informative letter, briefly explaining details of the planned intervention and essential study tasks. After written confirmation of participation in the study by interested GPs, the project assistants visit the participating GPs personally to explain the study design, provide study instruction and gain the GPs’ agreement to participate. In this context, a monetary incentive is provided to positively influence participation and cooperation [28–30]. Considering the experience of previous research for studies with relatively high workload for documentation, patient recruitment and study intervention, we expect a response-rate of 6 − 10 % [31, 32] for region B. Furthermore we expect, that the existing network structure in region A will generate a higher response rate.

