### Randomization

Participating clinics were randomly allocated to one of three study arms. A biometrician who is not involved in the field work, randomly selects the clinics. To avoid changes in physician’s prescription behavior, random lists remain concealed until each allocation date.

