### Statistical analyses

Baseline and demographic characteristics are analysed descriptively (number of valid cases, mean, standard deviation, minimum, median, lower and upper quartile, maximum for quantitative variables and number and proportions for qualitative variables).

The statistical analyses of the full-analysis set will follow the intention-to-treat (ITT) principle. This dataset includes all trial subjects who are randomized, meet all inclusion and exclusion criteria, have signed informed consent and have at least a baseline MAI score. Supportive analyses will be performed for the per-protocol (PP) population that includes all trial subjects of the ITT set who were treated as randomized and have at least two MAI scores after changing from control to intervention.

The primary hypothesis will be evaluated by a mixed model with treatment group and time as fixed effects and clustering structure as random effect. Significance level is set to alpha = 5 % (two-sided). It is assumed that values are missing at random (MAR) therefore no values need to be replaced in the mixed model. Secondary outcomes are analysed analogously. Further analyses are performed exploratory. In the sensitivity analysis missing values are replaced with last observation carried forward (LOCF).

Subgroup analyses will be performed with respect to age, gender, migrant status, social bonding and complexity of morbidity structure.

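### Two regions were chosen for their contrasting network structures, but the stated model and subgroup list leave region out, so no prespecified quantitative analysis takes it into account

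*Protocol article*

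**What the plan says.** Setting describes region A as a network of about 15 GPs and 18 specialists, and region B as an area of about 55 GPs with no network. It gives the contrast as the reason for the choice, which "enables us to measure performance and outcomes of the interprofessional medication therapy management approach while taking setting specific influence factors into account". The authors also expect the network to affect behaviour. For region B, "we expect a response-rate of 6 − 10 % [31, 32] for region B", and they expect a higher rate in region A.

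On allocation, Randomization says "Participating clinics were randomly allocated to one of three study arms", and Study design describes cluster randomisation of primary care units. Neither mentions region.

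Statistical analyses gives the primary model fixed terms for treatment and time and a random term for the clustering. On subgroups it says "Subgroup analyses will be performed with respect to age, gender, migrant status, social bonding and complexity of morbidity structure". All five are patient characteristics. It adds that unspecified further analyses will be exploratory.

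**The concern.** Network structure is the one feature for which the setting was selected, and the analysis section is specific enough to show that it is not used. Followed as written, the trial would report one pooled effect and no quantitative result by region. Any regional result that appeared later would be post hoc.

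There is a second, smaller issue. With 12 clinics, the three step groups can easily differ in regional mix. The model has one set of time effects for all clinics, so it assumes that networked and non-networked practices follow the same secular trend. If they do not, an uneven mix moves the estimated treatment effect.

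**Working it through.** **Inputs.** The Abstract describes a trial "involving 12 outpatient clinics (clusters) and 165 patients", or 165/12 = 13.75 patients per clinic. Sample size and power calculation gives an effect size of 0.25 and an ICC of 0.05. Its total reproduces: 502 × 0.383 = 192.3, and 192.3/0.80 = 240.3, about the stated 240. The plan gives no figure involving region. Assumptions made here: three groups of four clinics, one GP per clinic, and either 4 or 6 measurement periods.

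**Region-B clinics.** 0.06 × 55 = 3.3 and 0.10 × 55 = 5.5, so 3 to 6 clinics.

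**Chance of uneven mix without stratification.** With b region-B clinics, P(x, y, z) = C(4,x)·C(4,y)·C(4,z)/C(12,b), where x + y + z = b. The groups differ by at most one only in the most even pattern:

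| b | Most even pattern | Probability | Groups differ by 2 or more |
|---|---|---|---|
| 3 | 1,1,1 | 64/220 = 0.291 | 71% |
| 4 | 2,1,1 (3 orders) | 288/495 = 0.582 | 42% |
| 5 | 2,2,1 (3 orders) | 432/792 = 0.545 | 45% |
| 6 | 2,2,2 | 216/924 = 0.234 | 77% |

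The chance that at least one group comes wholly from one region is 71%, 42%, 21% and 14% respectively.

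**Effect on the primary estimate.** The model is a stepped-wedge mixed model with fixed period and treatment effects and a random clinic effect. The covariance of clinic-period means is ρJ + ((1−ρ)/n)I, with ρ = 0.05 and n = 13.75. Patient-level correlation over time is ignored. The standard error of the treatment effect is 0.134 SD with 4 periods and 0.1275 SD with 6. Averaged over all allocations, the shift due to region is zero. Its spread is:

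- *Stable regional difference, 6/6 split.* Per 1 SD of difference, the shift has an SD of 0.099 (4 periods) or 0.065 (6 periods), with a maximum of 0.267 or 0.176. If region explained the whole ICC, the difference would be 2√0.05 = 0.447 SD. The typical shift is then 0.447 × 0.065 to 0.447 × 0.099 = 0.03 to 0.04 SD, and the worst 0.447 × 0.176 to 0.447 × 0.267 = 0.08 to 0.12 SD.
- *Different linear trends, 3 to 6 region-B clinics.* For an illustrative regional divergence that reaches 1 SD by the end of the study, the typical shift is 0.04 to 0.06 SD and the worst 0.10 to 0.19 SD. Smaller divergences scale down in proportion.

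**What adding region would cost and give.**

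- A region main effect raises the standard error at most from 0.134 to 0.141 (4 periods) or from 0.1275 to 0.130 (6 periods). It removes a stable difference but not a differential trend.
- A condition-by-region interaction, with a 6/6 split balanced over steps, has a standard error of 0.162 or 0.136. Power for 0.25 SD is Φ(0.25/0.162 − 1.96) = 34% or Φ(0.25/0.136 − 1.96) = 45%. For 80% power the regional difference would have to be 2.80 × 0.162 = 0.45 SD or 2.80 × 0.136 = 0.38 SD. A more uneven split gives less power.

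**The case against.** The strongest reply is that no aim has been missed. None of the stated objectives, nor the primary hypothesis, compares regions, and Setting promises no interaction test and no causal attribution to network structure. The article does plan work on setting: a standardised questionnaire on physician and site factors (Data collection), practice characteristics and implementation barriers (Table 2), a quantitative and qualitative process evaluation, and open exploratory analyses. An article also condenses. Stratification by region may be described in a fuller document, and the random clustering term is not itemised.

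Much of this stands. A reader might infer that the plan cannot address setting at all. The documents do not support that: region is known for every clinic, and exploratory analysis is left open. A reader might also infer that region systematically confounds the step groups. That does not follow either. Allocation is random, so imbalance is chance error with mean zero. Every clinic supplies both control and intervention periods, which removes most of a stable regional difference. No passage indicates that the regional trends differ.

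The mismatch itself remains. The article does fix a model and name its subgroup factors, and it omits the factor for which the regions were chosen. None of the planned site-level work is tied to region.

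**Conclusion.** The point holds in a limited form. Setting presents the regional contrast as a way of measuring outcomes with setting taken into account, and no prespecified quantitative analysis in the article does so. The Setting wording is also too broad whatever analysis is added: one networked and one non-networked region cannot separate network structure from any other difference between the two areas.

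The threat to the primary result is modest. An uneven regional mix is likely (42% to 77%) if allocation was not stratified. The typical shift of 0.03 to 0.06 SD is small beside a standard error near 0.13 SD and a target effect of 0.25, although an unlucky allocation could reach 0.08 to 0.19 SD in the scenarios tried. These figures rest on equal groups of four, 3 to 6 region-B clinics (a 6/6 split for the stable difference), 4 or 6 periods, an ICC of 0.05, and a 1 SD divergence chosen only for illustration. The statement about allocation applies to this article alone.

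**What to change.** 1. In Statistical analyses, add region (A/B) to the subgroup factors as an exploratory condition-by-region interaction, with the effect and confidence interval for each region.
2. Add a sensitivity analysis of the primary model with region as a fixed effect and, if estimable, region-specific period effects. Only the latter addresses differing trends.
3. In Setting, limit the claim to a descriptive comparison of two regions.
4. In Randomization, state whether allocation was stratified by region.

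Trial status says that data cleaning and analysis have just started, so allocation cannot be changed. These analyses can still be fixed before results by region are seen. They need no new data. The cost is an imprecise interaction that must be labelled exploratory (34% to 45% power for 0.25 SD at best balance), a slightly larger standard error in the region-adjusted model, region-specific period effects estimated from perhaps only 3 to 6 region-B clinics, and a less ambitious sentence in Setting.
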